# **Study Protocol:**

## **The effects of trauma exposure on the brain, behavior, and cognition: A longitudinal neuroimaging study**

### **1. BACKGROUND**

Posttraumatic stress disorder (PTSD) is a psychiatric condition that can develop following exposure to traumatic events involving a serious threat to life, physical injury, or witnessing the death or suffering of others. Despite the widespread occurrence of trauma in the general population, only a subset of individuals develop PTSD, indicating that individual differences in neurobiological sensitivity and psychological resilience play crucial roles in determining clinical outcomes. Identifying the mechanisms underlying this variability remains a fundamental question in psychiatric neuroscience.

Previous neuroimaging studies have revealed alterations in brain networks involved in emotional regulation, threat detection, and stress reactivity in individuals with PTSD. These studies suggest that PTSD is associated with both functional and structural brain changes. However, most of this work has relied on cross-sectional data, making it difficult to determine whether the observed neural abnormalities precede the development of symptoms, result from trauma exposure, or persist as enduring traits in chronic cases. Without longitudinal evidence, it remains unclear whether these neural signatures represent markers of vulnerability, illness maintenance, or recovery.

The need for longitudinal research is particularly urgent in civilian trauma populations, which have received comparatively less attention than military or disaster-exposed cohorts. In everyday life, individuals are more likely to experience trauma through interpersonal violence, serious accidents, or medical crises rather than through war or large-scale disasters. Nevertheless, most existing PTSD studies have focused on highly specific groups, limiting their applicability to broader civilian populations. Furthermore, developmental aspects of trauma responses remain underexplored. Adolescents and young adults, whose brains are still undergoing rapid maturation, may be particularly vulnerable to long-term neurobiological consequences of trauma exposure, or alternatively, may exhibit unique patterns of resilience.

Emerging evidence, including our own prior work, suggests that changes in neurochemical signaling and cerebral blood flow within stress-regulatory brain regions may contribute to differences in clinical trajectories following trauma. Such changes may serve as potential biomarkers for identifying individuals at risk for chronic PTSD or those likely to experience spontaneous recovery. However, these findings require validation in large, systematically studied civilian samples using multimodal brain imaging and repeated longitudinal assessments over time.

## **2. OBJECTIVES OF STUDY**

This naturalistic observational study aims to investigate the biological and psychological mechanisms underlying the development and recovery of PTSD in a civilian sample following exposure to various traumatic events. Through comprehensive longitudinal assessments of brain structure and function, behavior, and cognition in trauma-exposed individuals, the study seeks to identify key factors contributing to individual differences in clinical outcomes. Specifically, the study will examine neuroimaging characteristics, psychosocial influences, peripheral blood-based biomarkers, and genetic predispositions that are associated with the onset, persistence, or remission of PTSD.

The ultimate goal of this study is to elucidate the pathophysiological mechanisms of PTSD and to discover predictive and protective factors that may inform the development of early diagnostic tools and more effective, biologically grounded treatments.

## **3. STUDY DESIGN**

This study is a naturalistic observational study involving adults and adolescents with and without trauma exposure. Participants will be recruited into trauma-exposed and trauma-unexposed groups.

At baseline, all participants will undergo comprehensive multi-modal neuroimaging, neurophysiological, clinical, and cognitive assessments. Follow-up evaluations will be conducted flexibly, adapting to the natural course of participant engagement and clinical needs. While we aim for periodic assessments, including potential evaluations around 3 months, 6 months, 1 year,

2 years, within 5 years, and within 10 years, the precise timing and frequency of these follow-ups will depend on individual participant availability and consent, reflecting the real-world nature of this study. The same protocols as baseline will be utilized for all follow-up assessments to ensure consistency.

## **4. STUDY POPULATION**

### **4.1. Participant Eligibility Criteria**

To participate in this study, individuals must meet the following criteria:

- (1) Age: Male and female participants aged 12 to 65 years old
- (2) Consent: Provided written consent to participate in the study
- (3) Trauma exposure:
  - Trauma-exposed group: Individuals who have experienced traumatic events, defined according to the criteria for Criterion A (Exposure to a Traumatic Event) in the Diagnostic and Statistical Manual of Mental Disorders (DSM)
  - Trauma-unexposed group (healthy control group): Individuals who have not experienced traumatic events

### **4.2. Exclusion Criteria**

Individuals will be excluded from the study if they meet any of following criteria:

- (1) For all participants: Presence of significant or unstable medical conditions necessitating hospitalization or surgical intervention
- (2) For the Trauma-unexposed group only:
  - Diagnosis of any psychiatric disorder
  - History of at least one major depressive episode within the past 12 months prior to enrollment
  - Current diagnosis of alcohol or other substance dependence
- (3) For participants undergoing neuroimaging assessments only:
  - Pregnancy or lactation

- History of neurological abnormalities or physical conditions known to affect brain imaging data, such as traumatic brain injury, epilepsy, multiple sclerosis, brain tumors, or cerebrovascular disease
- Any contraindications to magnetic resonance imaging (MRI) procedures, including severe claustrophobia or the presence of metal implants
- Use of psychotropic medications which can affect neuroimaging within the past three months (specific to trauma-unexposed participants)

### **4.3. Withdrawal Criteria**

Participant will be withdrawn from the study if he/she meets any of the following conditions:

- (1) Violation of the inclusion criteria: The participant is found to have violated any of pre-defined inclusion criteria.
- (2) Participant request: The participant requests to withdraw from the study.
- (3) Fulfillment of exclusion criteria: The participant subsequently meets any of the exclusion criteria (e.g., development of a new, severe, major physical illness).
- (4) Investigator discretion for safety: The investigator deems it necessary for the participants' safety.
- (5) Significant non-compliance: The participant demonstrates a significant degree of non-compliance with study procedures.
- (6) Loss to follow-up: The participant is lost to contact, making longitudinal follow-up impossible.

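### Section 4.3(3) with 4.2(2) withdraws controls who develop a psychiatric disorder but keeps exposed participants who do, so the longitudinal group contrast rests on controls selected for staying well

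*Protocol*

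**What the plan says.** Section 4.3 is mandatory and covers the whole study: "Participant will be withdrawn from the study if he/she meets any of the following conditions". Its third item applies when "The participant subsequently meets any of the exclusion criteria". A new serious physical illness is given there, but only as an example.

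Section 4.2(2) lists criteria headed "For the Trauma-unexposed group only". Two of them have no time anchor and can be met during follow-up: "Diagnosis of any psychiatric disorder" and "Current diagnosis of alcohol or other substance dependence". The third, a recent major depressive episode, is tied to the period before enrolment. Section 4.2(3) adds criteria for participants who are imaged. Among these are "Pregnancy or lactation" and, for controls only, recent psychotropic medication.

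Section 4.1 defines the comparator as "Trauma-unexposed group (healthy control group): Individuals who have not experienced traumatic events". Section 3 plans follow-up at about 3 months, 6 months, 1 year and 2 years, then within 5 and within 10 years. Section 2 makes the onset, persistence and remission of PTSD objects of study. Section 6.1(2) uses repeated measures ANCOVA or linear mixed-effects models and describes them as robust to missing data.

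**The concern.** The event that ends follow-up in one group is an outcome of the study, and in the other group the same event has no effect on follow-up. As the years pass, the remaining controls are increasingly those who stayed well, while the exposed group keeps its full mix of well and ill. Any measure that moves with psychiatric illness will then show a between-group difference in change that comes partly from the withdrawal rule.

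The Background criticises cross-sectional work for "making it difficult to determine whether the observed neural abnormalities precede the development of symptoms, result from trauma exposure, or persist as enduring traits". A control scanned before any trauma who later develops PTSD bears directly on that question. If such a person is still classed as a control at diagnosis, the rule ends their follow-up at that point.

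**Working it through.** The protocol states no sample size, incidence, effect size or dropout rate, so it has no figure of its own to reproduce. The first step is a reading of the text. The other two are illustrations on assumed inputs.

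**Step 1: what happens to the same new diagnosis in each group**

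| New event during follow-up | Unexposed control | Exposed participant |
|---|---|---|
| Any psychiatric disorder | Meets 4.2(2), withdrawn under 4.3(3) | Meets no exclusion, stays |
| Substance dependence | Meets 4.2(2), withdrawn | Meets no exclusion, stays |
| Starts psychotropic medication, if imaged | Meets 4.2(3), withdrawn on a literal reading | Item does not apply, stays |
| Major depressive episode item | Tied to enrolment, cannot be met later (the episode still counts as a psychiatric disorder) | Does not apply |
| Serious medical condition | Meets 4.2(1) | Meets 4.2(1) |

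The first three rows are asymmetric. No text reclassifies the withdrawn controls or keeps them under observation.

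**Step 2: size of the shift in the control mean**

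Assumed: annual incidence *r* of 2% to 5% in controls, a shift *d* of 0.3 to 0.5 SD in those who fall ill, no recovery, full attendance otherwise, and no data from the ill visit.

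Share withdrawn by year *t* = 1 − (1 − *r*)^*t*. Error in the control mean = share × *d*.

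- Year 2, low: 1 − 0.98² = 0.0396; × 0.3 = 0.012 SD.
- Year 2, high: 1 − 0.95² = 0.0975; × 0.5 = 0.049 SD.
- Year 10, low: 1 − 0.98¹⁰ = 0.183; × 0.3 = 0.055 SD.
- Year 10, high: 1 − 0.95¹⁰ = 0.401; × 0.5 = 0.20 SD.

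**Step 3: does the planned mixed model remove it?**

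A random-intercept model was simulated with 5 visits, 4,000 per group and within-person correlation 0.6. Cumulative incidence *p* was the same in both groups, so the true contrast is zero. Entries are the group-by-last-visit contrast in SD, one run per cell, standard error 0.020 to 0.022.

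| *p* | *d* | Ill controls kept | Withdrawn before the ill visit | Withdrawn after the ill visit |
|---|---|---|---|---|
| 10% | 0.5 | −0.010 | 0.055 | 0.061 |
| 10% | 1.0 | −0.051 | 0.114 | 0.046 |
| 20% | 0.5 | 0.010 | 0.116 | 0.066 |
| 20% | 1.0 | 0.004 | 0.209 | 0.101 |
| 30% | 0.5 | 0.006 | 0.166 | 0.073 |
| 30% | 1.0 | 0.043 | 0.319 | 0.123 |

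With ill controls kept, the contrast scatters around zero. The two largest departures are −0.051/0.021 = −2.4 and 0.043/0.021 = 2.0 standard errors, in opposite directions, so small entries should not be read finely. With withdrawal before the ill visit, the contrast is close to *p* × *d*, because the values that drive the withdrawal are never observed. Recording the ill visit reduces the bias in five of the six settings but does not remove it. The exception (0.061 against 0.055) is within simulation noise.

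**The case against.** The strongest reply is that the rule reaches less far than it first appears, and much of that reply stands.

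- **Newly traumatised controls.** A reader might infer that every control who is traumatised and develops PTSD is removed. The text does not establish this. Under 4.1 such a person now fits the exposed definition, in which case 4.2(2) no longer applies. The inclusion-violation item in 4.3(1) reads most naturally as covering errors at entry. The protocol does not settle the person's classification.
- **Loss of pre/post-trauma data.** It is tempting to say that nearly all of it goes. At most, follow-up is lost for controls who fall ill while still classed as controls. Nothing says that data already collected are discarded. Exposed participants scanned before symptoms begin also bear on the Background's question.
- **Direction.** A reader might infer that the bias always enlarges the group difference. It pushes the exposed-minus-control contrast in the direction of the illness effect. Where the true exposure difference runs the other way it shrinks the contrast, and the Background itself allows for resilience. Measures unrelated to illness are not biased.
- **Pregnancy and other imaging items.** These apply only to participants being imaged, and section 5 makes each assessment depend on feasibility. That pregnancy ends all participation is one literal reading, not a settled rule.
- **Aims.** Contrasts within the exposed group are untouched, no primary group-by-time contrast is named, and four of the six planned timepoints fall at or before year 2, where the shift is small.
- **Comparator.** Controls are labelled healthy, so a stay-healthy reference may be intended. The protocol does not say so, and that would be a different estimand, conditioned on the future.

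None of this cures the central case: a still-unexposed control with a new disorder must leave. Coding of groups can be left to a statistical analysis plan, but no analysis plan can restore follow-up that was never collected.

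**Conclusion.** Wrong as written, for incident psychiatric disorder and substance dependence in controls. Sections 4.2(2) and 4.3(3) together make withdrawal depend on both group and outcome, and the models in 6.1(2) do not correct for it.

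The size cannot be derived from the documents. The Step 2 range, from about 0.01 SD at the low end of year 2 to about 0.20 SD at the high end of year 10, rests entirely on the assumed incidence and illness effect. It would be smaller with recovery or with the first ill visit recorded. The bias is small if few controls fall ill.

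Two related points are ambiguities to be resolved and not demonstrated losses: the status of a control traumatised during follow-up, and whether an imaging-only criterion ends study participation.

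**What to change.** 1. State in 4.3(3) that the 4.2(2) criteria, and the control-only psychotropic medication item in 4.2(3), are judged at enrolment to decide group membership and do not end follow-up.
2. Keep controls with an incident disorder in follow-up and analyse them in the group they entered. Add a sensitivity analysis restricted to controls who remain healthy.
3. Keep controls with incident trauma in follow-up and code exposure as time-varying from the event date.
4. Reconcile 4.3(3) with the imaging-only scope of 4.2(3) and the feasibility wording of section 5, so that an imaging-only criterion decides whether a scan is done and not whether the person remains in the study.
5. Leave the physical-illness and safety withdrawal rules as they stand. This point gives no reason to change them.

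The cost is a wording amendment and one time-varying exposure variable. Section 5 already repeats the trauma assessment, the SCID and the CAPS at follow-up, so no new assessments are needed. The drawback is that the control group becomes less purely healthy over time, which the sensitivity analysis in item 2 addresses.

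### Exclusion criteria that apply to controls only also act as withdrawal rules, so unexposed participants leave on developing a disorder while exposed participants stay, which can bias the contrast of longitudinal change

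*Protocol*

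**What the plan says.** Protocol 4.3 makes withdrawal mandatory and study-wide: "Participant will be withdrawn from the study if he/she meets any of the following conditions". Condition (3) is "The participant subsequently meets any of the exclusion criteria". A physical illness is given as an example and does not limit the rule.

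Protocol 4.2 sets different exclusions for the two groups. Under "For the Trauma-unexposed group only" it lists "Diagnosis of any psychiatric disorder", a major depressive episode in the 12 months before enrolment, and "Current diagnosis of alcohol or other substance dependence". Under the criteria for participants having neuroimaging it adds "Use of psychotropic medications which can affect neuroimaging within the past three months (specific to trauma-unexposed participants".

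Nothing in 4.2 or 4.3 says that the psychiatric, dependence or psychotropic criteria stop applying after entry. Sections 3 and 4.1 define the groups at recruitment. They give no rule for a control who has a Criterion A event later.

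Section 3 foresees follow-up to within 10 years, and section 5 repeats the SCID, CAPS and questionnaires at follow-up as feasible. Section 6.1(2) plans repeated measures ANCOVA or linear mixed-effects models and describes them as robust to missing data.

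**The concern.** The events that remove a control are outcomes the study measures: psychiatric diagnosis, depression, alcohol use and PTSD. The same events do not remove an exposed participant. Over a long follow-up the remaining controls are increasingly those who stayed well, while the exposed group keeps its new cases. Even if trauma had no effect on change, the exposed could then appear to do worse over time.

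A mixed model is valid when dropout can be explained by recorded data. It does not cover values that go missing because of an onset that the recorded data do not show.

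A second issue concerns PTSD onset. Section 1 faults cross-sectional work for "making it difficult to determine whether the observed neural abnormalities precede the development of symptoms, result from trauma exposure, or persist as enduring traits", and section 2 makes onset an objective. A control who has a first trauma and then PTSD has assessments before both. PTSD is a psychiatric disorder, so this person may be withdrawn just when the later data become useful.

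**Working it through.** **Step 1: which criteria can newly trigger withdrawal, and for whom.**

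| Criterion in 4.2 | Applies to | Can it be newly met in follow-up? |
|---|---|---|
| Any psychiatric disorder | Controls | Yes |
| Current substance dependence | Controls | Yes |
| Major depressive episode in the 12 months before enrolment | Controls | No, it is tied to enrolment; a new episode falls under psychiatric disorder |
| Psychotropics that can affect imaging, past three months | Controls having neuroimaging | Yes, for those controls |

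Section 3 says all participants are imaged at baseline. Section 5 makes imaging subject to consent and feasibility, so the last row covers imaged controls and not necessarily every control.

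**Step 2: inputs for size.** The protocol states no sample size, SD, effect size, incidence or dropout rate, so there is no figure to reproduce. Everything below is assumed: 150 per group, the same true incidence of new disorder in both groups, no true group difference, and an outcome SD of about 1 that shifts by d from onset.

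**Step 3: closed form.** With annual incidence λ, the share of controls removed by year t is p = 1 − (1 − λ)^t. If no post-onset value is recorded, the mean of the remaining controls is off by p × d.

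- λ = 1%, 3%, 5%: p = 4.9%, 14.1%, 22.6% at 5 years and 9.6%, 26.3%, 40.1% at 10 years.
- At 10 years with λ = 3% and d = 0.5: 0.263 × 0.5 = 0.13 SD.
- With a constant hazard of 2% or 4% per year, controls left at 5 years are 150 × exp(−0.10) = 136 or 150 × exp(−0.20) = 123.

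**Step 4: simulation, permanent shift, diagnosis visit not recorded.** The model is y ~ group × time. The 5-year rows use a random intercept and slope, with visits at 0, 3, 6, 12, 24 and 60 months and 120 runs. The 10-year rows use a random intercept, with a visit added at 10 years and 150 runs.

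| Horizon | λ per year | d (SD) | False difference in change (SD) | Rejection at 5% |
|---|---|---|---|---|
| 5 y | 2% | 1.0 | 0.095 | 20% |
| 5 y | 2% | 1.5 | 0.142 | 34% |
| 5 y | 4% | 1.0 | 0.176 | 45% |
| 5 y | 4% | 1.5 | 0.264 | 73% |
| 10 y | 3% | 0.5 | 0.136 | 29% |
| 10 y | 5% | 0.5 | 0.194 | 52% |
| 10 y | 3% | 0.8 | 0.201 | 57% |

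The closed form agrees. For the first row, (1 − exp(−0.10)) × 1.0 = 0.095. A repeat of the 5-year extremes with 200 runs gave 0.09 SD with 18.5% and 0.27 SD with 73.5%.

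**Step 5: the same, with the diagnosis visit recorded before withdrawal.** The 5-year settings give 0.029-0.066 SD and 8-9% rejection; the repeat gave 0.02-0.06 SD and 8-12%. The three 10-year settings give 0.047, 0.051 and 0.076 SD, with 7%, 9% and 13%. Monte Carlo error at a true 5% is √(0.05 × 0.95/120) = 2.0 percentage points for 120 runs.

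**Step 6: milder assumptions, diagnosis visit not recorded.**

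- d = 0.3, λ = 2%, 5 years: 0.03 SD, 8% rejection.
- Mean episode of 1 year, d = 1.0, controls withdrawn only if ill at a visit: 0.01 SD with 3.0% (λ = 2%) and 0.02 SD with 6.5% (λ = 4%).

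**The case against.** The only example in 4.3(3) is a physical illness, and section 4.1 calls the unexposed a healthy control group. The sponsor may not have meant the psychiatric trigger, or may want a healthy reference trajectory. That is a defensible comparator. Still, the text says any exclusion criterion, and sites follow the text. A healthy reference can be recovered by dropping post-onset visits at analysis, whereas visits never made cannot be recovered.

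A reader might infer from Step 4 that the main contrast is badly anti-conservative. The documents do not support that. Section 5 places the diagnostic interview among the follow-up assessments, and 4.3 does not say that data from that visit or earlier are discarded. A diagnosis made at a study visit would normally come with data, which points to Step 5. Permanent disorder is also only an assumption, and section 2 names remission as an object of study. Nor do the documents support shifts of 1.0-1.5 SD for brain or cognitive measures.

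A reader might also infer that 4.3(3) alone removes the only cases able to show whether abnormalities precede symptoms. Two points count against this. Exposed participants scanned before PTSD onset also inform that question, and they are unaffected. And a control with a Criterion A event no longer fits the control definition. That person might count as exposed, so that the control-only criteria lapse, or might be removed under 4.3(1). The loss comes from 4.3(1), 4.3(3) and the missing crossover rule together.

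**Conclusion.** The asymmetry stands on the wording of 4.2 and 4.3. Controls are withdrawn for incident psychiatric disorder or substance dependence, and imaged controls also for relevant psychotropic use, while exposed participants with the same events stay. The exposed-versus-unexposed contrast of change can therefore be biased towards worse change in the exposed. Baseline comparisons and analyses within the exposed group are not touched.

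The size rests on assumptions the protocol does not supply:

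- **Diagnosis visit recorded:** about 0.02-0.08 SD, with 7-13% rejection at a nominal 5%.
- **Worst case, visit not recorded and disorder permanent:** up to about 0.10-0.26 SD, with 20-73% rejection.
- **Short episodes:** near zero.

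Controls with a first trauma and then PTSD have assessments before both, and the protocol leaves open whether they are kept. It does not say outright that they are lost, nor that data already collected are discarded.

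This is a cheap improvement, not a fatal fault. It belongs in the protocol because a later analysis plan cannot restore visits that were not made.

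**What to change.** 1. Amend 4.3 so that the control-only criteria, meaning 4.2(2) and the control-only psychotropic criterion in 4.2(3), apply at enrolment only.
2. Keep a control with later onset of disorder, dependence or medication use in follow-up on the same terms as everyone else. Record the onset date and keep this person in the main longitudinal comparison.
3. Add a sensitivity analysis that drops control visits after onset. This gives the healthy-reference comparison for those who want it.
4. State in 4.3(1) and 4.3(3) that a control with a new Criterion A event is not withdrawn, but followed and analysed as an incident-exposure case with pre-trauma data. Changing 4.3(3) alone would not secure these cases.

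The cost is a few sentences in the protocol, one sensitivity analysis, and follow-up visits for controls who would otherwise have left. The small downside is that some later control scans will be on medication; the sensitivity analysis handles this.

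### Protocol 4.3(3) makes any later medical condition needing hospital care or surgery a mandatory exit from the whole study, with no pause or return, over up to 10 years of observational follow-up

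*Protocol*

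**What the plan says.** Section 4.3 of the protocol is mandatory and acts on the whole study, not on a single visit or procedure: "Participant will be withdrawn from the study if he/she meets any of the following conditions". Its third condition is that any one of the exclusion criteria is met after enrolment, and the example it gives is "development of a new, severe, major physical illness".

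Of the exclusions in section 4.2, only the first applies to everyone: "Presence of significant or unstable medical conditions necessitating hospitalization or surgical intervention". The others are limited to the unexposed group or to participants having neuroimaging.

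Section 3 plans assessments at about 3 months, 6 months and 1 year, and then at "2 years, within 5 years, and within 10 years, the precise timing and frequency of these follow-ups will depend on individual participant availability and consent". Section 5 repeats the baseline battery at follow-up where feasible. The battery includes the history of traumatic events and whether they involved physical injury.

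Safety has its own withdrawal condition, 4.3(4): "The investigator deems it necessary for the participants' safety".

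**The concern.** A screening criterion has become a continuous removal rule. At enrolment, 4.2(1) sensibly defers someone who is acutely ill. Carried into follow-up by 4.3(3), the same words remove a participant who is admitted or operated on at any point in a decade, even if the condition resolves within weeks.

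The study gives no treatment that would have to be stopped. What is lost is observation, and the loss is tied to a health event that may be related to trauma and to the course of PTSD. Some of these events will be injuries or medical crises of the kind that section 1 lists when it says "individuals are more likely to experience trauma through interpersonal violence, serious accidents, or medical crises". Dropout of this kind may be informative.

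Section 6.1(2) relies on repeated measures ANCOVA or linear mixed-effects models and calls them robust to missing data. A likelihood-based mixed model can use the visits before withdrawal. It is valid if missingness depends only on what was observed, but not if it depends on outcomes that were never seen. No analysis plan can restore visits that the protocol itself cancels.

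**Working it through.** The protocol states no sample size, dropout rate or hospitalization rate, so there is no figure of its own to reproduce. The check has two parts.

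**1. The text chain**

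| Step | Source | Content |
|---|---|---|
| Force of the rule | 4.3, opening line | Withdrawal is compulsory and is from the study |
| Trigger | 4.3(3) | Any exclusion criterion met after enrolment |
| Criterion reaching all participants | 4.2(1) | A present medical state needing admission or an operation; no minimum duration |
| Time at risk | 3 | Up to 10 years |
| Way back | 3, 4.3 and 5 | No pause, re-entry or assessment-level exemption for this trigger |
| Room for a milder rule | 3 and 5 | Visit timing is already flexible; assessments are done as feasible |
| Safety | 4.3(4) | Covered separately |

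The example in 4.3(3) is narrower than 4.2(1), but it is introduced as an example and does not limit the reference to every exclusion criterion. Read literally, the chain ends all follow-up at the first qualifying event.

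**2. Scale, under an assumed rate**

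Let *h* be the yearly probability that a participant still in follow-up first meets 4.2(1). Assume that it is constant, that the rule is applied literally, and that nobody leaves for another reason. The cumulative share withdrawn by year *t* is 1 − (1 − *h*)^*t*.

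| Assumed *h* | By year 5 | By year 10 |
|---|---|---|
| 2% | 1 − 0.98^5 = 9.6% | 1 − 0.98^10 = 18.3% |
| 5% | 1 − 0.95^5 = 22.6% | 1 − 0.95^10 = 40.1% |
| 8% | 1 − 0.92^5 = 34.1% | 1 − 0.92^10 = 56.6% |

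A wider assumption of 1% to 10% per year gives 9.6% to 65.1% by year 10. These figures show scale only. Because attendance is voluntary, some participants will leave for other reasons first, so the share removed by this rule would be lower than shown at any given *h*.

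**The case against.** The strongest reply is that the sponsor means something milder. The criterion is confined to serious or unstable conditions, and the only example is "development of a new, severe, major physical illness", which suggests grave and lasting disease, not any admission. The protocol does not call the withdrawal permanent; that is inferred from the absence of a return rule. This stands as a limit on what can be claimed, but it does not remove the problem. The text gives no milder rule, so sites must either apply it as written or diverge.

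A second reply is that severe illness or surgery can distort imaging, heart rate variability, cognition and blood markers. That is a fair reason to postpone or flag an assessment. It is not a reason to end the participant's whole follow-up.

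Three stronger readings are tempting, and the documents do not support them.

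- *Follow-up ends at the very events the study sets out to observe.* The objective in section 2 concerns mechanisms "underlying the development and recovery of PTSD in a civilian sample following exposure to various traumatic events". New traumas during follow-up are not a named target. Section 1 is background, and section 5 asks about lifetime events.
- *Any new accident or assault triggers the rule.* Under 4.2(1), only one that leaves a condition needing hospital care or surgery does.
- *Remission will be overstated.* This depends entirely on who is lost. Take a true remission of 50%, with assumed yearly loss of 3% in remitters and 6% in the others. The share remitted among those remaining at 5 years is 0.97^5 / (0.97^5 + 0.94^5) = 0.859 / (0.859 + 0.734) = 53.9%. With the rates exchanged it is 46.1%, and with equal rates it stays at 50%. The protocol supplies none of these inputs and defines no remission proportion as an endpoint.

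**Conclusion.** The point holds in a limited form. As written, 4.3(3) together with 4.2(1) compels withdrawal from the entire study when a participant meets the medical criterion at any time in up to 10 years, and the protocol provides no pause, partial assessment or return. This does not fit a naturalistic study with flexible visits, and it needlessly discards follow-up after events that may be transient.

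The loss may be informative, and the planned models do not protect against missingness that depends on unobserved outcomes. The direction and size of any bias cannot be stated from the document. The only quantity offered is the share withdrawn: about 10-34% by year 5 and 18-57% by year 10, resting on an assumed 2-8% per year, a constant rate, literal application of the rule and no other loss.

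This is a stated rule that produces a worse result than an easy alternative, not a detail left to a later document. It should be changed, with moderate confidence about how much it matters in practice.

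**What to change.** Amend 4.3(3) so that criterion 4.2(1) applies at enrolment. If a participant meets it later:

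- postpone or skip the affected assessments;
- record the event and its date, so that affected data can be flagged or adjusted for in the analysis;
- keep the participant in follow-up.

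Leave 4.3(1), (2), (4), (5) and (6) as they are. Withdrawal for inclusion violations, participant request, safety, non-compliance and loss of contact is not in question here. Because 4.3(3) also carries 4.2(2) and 4.2(3) into follow-up, the amended text should make clear that this change concerns 4.2(1) only.

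The cost is a short protocol amendment, some delayed visits (which section 3 already accommodates), one extra data item, and some assessments after illness that need flagging or a sensitivity analysis.
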